## **7.10 Pharmacogenetics/pharmacogenomics**

None.

## **7.11 Other biomarkers**

Assessment of basiliximab concentration as well as lymphocyte immunophenotyping may be performed by some of the sites.

For the analysis of basiliximab serum concentration 1 ml venous blood samples should be collected before randomization and on week 12 prior to basiliximab injection. Analysis will be performed using ELISA method. An average serum basiliximab concentration of 0.2 µg/ml is referred to as sufficient to saturate CD25 on peripheral blood lymphocytes ([Hoecker et al., 2008](#); [Kovarik et al., 1999](#))

Analysis of 0.5 ml venous blood will be performed for lymphocyte immunophenotyping. Therefore monoclonal antibodies against two IL-2R $\alpha$  regions - epitope A which is basiliximab blocked and epitope B which is not bound by basiliximab – will be used to investigate the course of CD25+ T lymphocyte fraction after basiliximab injection ([Hoecker et al., 2008](#)).

All samples will be frozen and will be measured in a center laboratory.

## **7.12 Additional Assessments**

Further assessments that might be of interest (e.g., Quality of Life, biopsies, etc.) may be performed by some of the sites. The assessment of further parameters may be fixed in additional site specific protocols. Except for the indicated time points (null biopsy and biopsies at Week 7 and 24) no further protocol biopsies are recommended.

The additional protocols will be submitted for review and approval to the responsible ethics committee prior to implementation.

## **8 Safety monitoring**

### **8.1 Serious adverse event reporting**

To ensure patient safety, every SAE, regardless of suspected causality, occurring after the patient has provided informed consent and until 30 days after the patient has stopped study participation (defined as time of last dose of study drug taken) must be reported to Novartis within 24 hours of learning of its occurrence. Any SAEs experienced after this 4-week period should only be reported to Novartis if the investigator suspects a causal relationship to the study drug. Recurrent episodes, complications, or progression of the initial SAE must be reported as follow-up to the original episode within 24 hours of the investigator receiving the follow-up information. An SAE occurring at a different time interval or otherwise considered completely unrelated to a previously reported one should be reported separately as a new event.

Information about all SAEs is collected and recorded on the Serious Adverse Event Report Form. The investigator must assess the relationship to study drug, complete the SAE Report Form in English, and send the completed, signed form by fax within 24 hours to the local Novartis Clinical Safety & Epidemiology Department. The telephone and telefax number of the contact persons in the local department of Clinical Safety and Epidemiology, specific to the site, are listed in the investigator folder provided to each site. The original copy of the SAE Report Form and the fax confirmation sheet must be kept with the case report form documentation at the study site.

Follow-up information is sent to the same person to whom the original SAE Report Form was sent, using a new SAE Report Form stating that this is a follow-up to the previously reported SAE and giving the date of the original report. Each re-occurrence, complication, or progression of the original event should be reported as a follow-up to that event regardless of when it occurs. The follow-up information should describe whether the event has resolved or continues, if and how it was treated and whether the patient continued or withdrew from study participation.

If the SAE is not previously documented in the Investigator's Brochure or Package Insert (new occurrence) and is thought to be related to the Novartis study drug, a Clinical Safety & Epidemiology Department associate may urgently require further information from the investigator for Health Authority reporting. Novartis may need to issue an Investigator Notification (IN), to inform all investigators involved in any study with the same drug that this SAE has been reported.

### **8.2 Pregnancies**

To ensure patient safety, each pregnancy in a patient on study drug must be reported to Novartis within 24 hours of learning of its occurrence. The pregnancy should be followed up to determine outcome, including spontaneous or voluntary termination, details of the birth, and the presence or absence of any birth defects, congenital abnormalities, or maternal and/or newborn complications.

Pregnancy should be recorded on a Clinical Trial Pregnancy Form and reported by the investigator to the local Novartis Clinical Safety & Epidemiology Department. Pregnancy follow-up should be recorded on the same form and should include an assessment of the possible relationship to the Novartis study drug of any pregnancy outcome. Any SAE experienced during pregnancy must be reported on the SAE Report Form.

### **8.3 Data Safety Monitoring Board**

An external and independent Data Safety Monitoring Board (DSMB) will be instituted before study start. The DSMB will review safety-related issues and will be entitled to make recommendations for changes in study conduct. Details on the function of the DSMB will be laid out in a separate DSMB Charter.

## **9 Data review and database management**

### **9.1 Site monitoring**

Before study initiation, at a site initiation visit or at an investigator's meeting, a Novartis representative will review the protocol and CRFs with the investigators and their staff. During the study, the field monitor will visit the site regularly to check the completeness of patient records, the accuracy of entries on the CRFs, the adherence to the protocol and to Good Clinical Practice, the progress of enrollment, and to ensure that study drug is being stored, dispensed, and accounted for according to specifications. Key study personnel must be available to assist the field monitor during these visits.

The investigator must maintain source documents for each patient in the study, consisting of case and visit notes (hospital or clinic medical records) containing demographic and medical information, laboratory data, electrocardiograms, and the results of any other tests or assessments. All information on CRFs must be traceable to these source documents in the patient's file. Data not requiring a separate written record will be defined before study start and will be recorded directly on the CRFs, which will be documented as being the source data. The investigator must also keep the original informed consent form signed by the patient (a signed copy is given to the patient).

The investigator must give the monitor access to all relevant source documents to confirm their consistency with the CRF entries. Novartis monitoring standards require full verification for the presence of informed consent, adherence to the inclusion/exclusion criteria, documentation of SAEs, and the recording of data that will be used for all primary and safety variables. Additional checks of the consistency of the source data with the CRFs are performed according to the study-specific monitoring plan. No information in source documents about the identity of the patients will be disclosed.

## **9.2 Data collection**

Designated investigator staff must enter the information required by the protocol onto the Novartis CRFs that are printed on 3-part, non-carbon-required paper. Field monitors will review the CRFs for completeness and accuracy and instruct site personnel to make any required corrections or additions. The CRFs are forwarded to Data Management by field monitors, one copy being retained at the investigational site. Once the CRFs are received by Data Management, their receipt is recorded and they are reviewed prior to data entry.

## **9.3 Database management and quality control**

Data from the CRFs are entered into the study database by Contract Research Organization staff following their own internal standard operating procedures that have been reviewed and approved by Novartis.

Subsequently, the entered data are systematically checked by Data Management staff, using error messages printed from validation programs and database listings. Obvious errors are corrected by Data Management personnel. Other errors or omissions are entered on Data Query Forms, which are returned to the investigational site for resolution. The signed original and resolved Data Query Forms are kept with the CRFs at the investigator site, and a copy is sent to Novartis so the resolutions can be entered into the database. Quality control audits of all key safety and efficacy data in the database are made prior to locking the database.

Concomitant medications entered into the database will be coded using the WHO Drug Reference List, which employs the Anatomical Therapeutic Chemical classification system. Medical history/current medical conditions and adverse events will be coded using the Medical dictionary for regulatory activities (MedDRA) terminology.

At the conclusion of the study the database has been declared to be complete and accurate and will be locked. Any changes to the database after that time can only be made by joint agreement between the Trial Statistician and Statistical Reporting and the Clinical Trial Leader.

## **10 Statistical methods**

The data will be analyzed by Novartis and/or by the designated CRO. Any data analysis carried out independently by the investigator(s) should be submitted to Novartis before publication or presentation. The final analysis will be done when all patients have completed the study treatment at Visit 6 (Week 24/Month 6) or discontinued prematurely. It is planned that the data from all centers that participate in this protocol will be used, so that an adequate number of patients will be available for analysis.

Data will be summarized with respect to demographic and baseline characteristics, efficacy observations and measurements, safety observations and measurements, and pharmacokinetic measurements. All summary statistics will be presented by

treatment group. Categorical variables will be summarized by absolute and relative frequencies. Continuous variables will be summarized by descriptive statistics of mean, standard deviation, minimum, median and maximum. Time-to-event data including rates of affected patients will be assessed by Kaplan-Meier statistics.

The assessment of safety will be based mainly on the frequency of adverse events and on the number of laboratory values that fall outside of pre-determined ranges. Other safety data (e.g. electrocardiogram, vital signs, special tests) will be considered as appropriate. Adverse events will be summarized by presenting, for each treatment group, the number and percentage of patients having any adverse event, having an adverse event in each body system and having each individual adverse event. Any other information collected (e.g. severity or relatedness to study medication) will be listed as appropriate.

## **10.1 Analysis set**

### **Randomized set**

The randomized set will consist of all patients who were randomized at Baseline Visit 2 (Visit 3/Week 7). Patients will be considered randomized when they have received a randomization number, and thus have been assigned to a treatment group. This does not necessarily mean that they have taken, or in fact have been administered, randomized medication.

### **Full analysis set**

The full analysis set (FAS) will consist of all patients randomized at Baseline Visit 2 (Week 7). Patients will be analyzed according to treatment assigned and their actual stratum. This set may include patients without any data after randomization (methods to account for missing data in the analysis are described in [Section 10.4.3](#) below).

### **Per-protocol set**

The per-protocol set will consist of a subset of patients of the FAS who did not show major deviations from the protocol procedures that may have an impact on the study outcome. Reasons for exclusion of the per-protocol set may be (but are not limited to): deviations from entry criteria, errors in treatment assignment, use of excluded/forbidden/un-allowed medication, premature discontinuation of randomized treatment or study, poor compliance, loss to follow-up, missing data in the primary efficacy variable. All criteria that are assumed to have such an impact will be defined before database lock during the central blinded review. The per-protocol set will be used for sensitivity analyses of the primary variable.

### **Safety set**

The safety set will consist of all patients in whom transplantation was performed and who received at least one dose of any immunosuppressive medication after

Baseline 1. Note: The statement that a patient had no adverse events constitutes a safety assessment.

### **Enrolled set**

The enrolled set will consist of all patients who gave informed consent. The enrolled set will be used for analysis of background and demographic characteristics to account for patients who were enrolled but failed to be randomized (and thus are not part of the FAS).

## **10.2 Background and demographic characteristics**

Demographic and background information will be summarized for the full analysis (FAS) and the enrolled set. Background information includes prior medication, past/current medical conditions and transplant history.

Medical history will be coded using MedDRA and will be presented by system organ class, MedDRA preferred term and treatment group. Separate tables will be provided for past medical condition and current medical condition. Prior medication will be coded according to WHO Drug Reference List.

## **10.3 Study treatments**

### **10.3.1 Study medication**

Duration (days) of exposure to each individual component of the immunosuppressive treatment regimen will be summarized. Dosage averages will be calculated including and excluding zero doses for periods of temporary interruption of treatment regardless of whether this was due to safety reasons or patients' non-compliance. Daily dose levels will be summarized with mean, standard deviation, minimum, median, and maximum by time interval. Frequencies of the number of patients with any dose reduction (including temporary dose interruption) as well as the number of dose reductions by reason will be given. These analyses will be performed for the safety and the full analysis sets.

### **10.3.2 Concomitant therapy**

Prior and concomitant medications and non-drug therapies will be coded according to WHO-DRL. Medications will be summarized by preferred term, ATC class and treatment group separately for medications either ending before start of study drug (prior medications) or concomitantly taken through the study (concomitant medications) for the safety set.

## **10.4 Analysis of the primary objective(s)**

The primary objective of this study is to demonstrate superior renal function under the Certican®-based regimen as compared to the control regimen.

#### 10.4.1 Variable

The primary variable for assessment of renal function is the glomerular filtration rate (GFR) at Month 6, as assessed by the Cockcroft-Gault method (recalculated values, see [Section 7.5](#)).

#### 10.4.2 Statistical hypothesis, model, and method of analysis

The null hypothesis of no difference in GFR at Month 6 between both treatment groups

$$H_0: \mu_{\text{Certican}} = \mu_{\text{Control}}$$

will be tested against the two-sided alternative hypothesis of different mean GFR at Month 6 of the Certican® compared to control regimen

$$H_1: \mu_{\text{Certican}} \neq \mu_{\text{Control}}$$

$\mu$  indicates the mean GFR at Month 6.

The hypotheses will be tested with an analysis of covariance (ANCOVA) with treatment, center, and occurrence of rejections before randomization as factors, and GFR at Visit 3 (Baseline 2) as covariate. Raw as well as adjusted means (= LS-means, LS: least square means) will be presented for the treatment contrast together with its confidence interval and a two-sided p-value. The significance level will be 5% (two-sided). The full analysis set (FAS) will be used for the primary analysis. There are no multiplicity issues to be addressed since only the hypothesis of superior efficacy of the Certican® vs. the control regimen will be tested confirmatorily.

#### 10.4.3 Handling of missing values/censoring/discontinuations with respect to the primary efficacy variable

If a patient discontinues from the study prematurely after Visit 3/Baseline 2, missing data with respect to the primary efficacy parameter will be imputed via multiple imputation. The multiple imputation procedure will be presented in detail (e.g. seed value, method for imputation) in the statistical analysis plan to be finalized before database lock.

Multiple imputation inference involves three distinct phases:

- The missing data are filled in  $m$  times to generate  $m$  complete data sets.
- The  $m$  complete data sets are analyzed according to the ANCOVA model.
- The results from the  $m$  complete data sets are combined for the inference.

For sensitivity, missing data will not be imputed but instead, a mixed model approach for repeated measures (MMRM) will be applied (see [Section 10.4.4](#) below).

#### 10.4.4 Supportive analyses

For sensitivity, the following analyses will be performed:

1. The primary analysis will be performed with the PP set. Missing values will be dealt by multiple imputation.

2. The primary analysis will be once more performed for the FAS after having imputed missing values by last observation carried forward (LOCF). If a patient discontinues from the study prematurely after Visit 3/Baseline 2, missing data with respect to the primary efficacy parameter will be substituted by the last recorded value (last observation carried forward, LOCF). The last observation will only be carried forward if a patient has had at least one assessment after BL2, i.e. on Visits 4 to 6. Under the assumption that the GFR will remain fairly stable in the control group but will probably improve in the Certican group, this strategy corresponds to a conservative estimate of the therapy effect within both treatment groups.
3. For sensitivity, the primary efficacy variable will be analyzed using a mixed model for repeated measures (MMRM) approach to deal with missing values occurring after Visit 3 (Week 7/Baseline 2). This analysis will be performed for the FAS.

The course of the GFR will be summarized by visit and treatment group. Changes from BL2 to each post-baseline measure will be calculated by treatment group for each study visit. If patients of the FAS are switched from the control to the Certican group during the study, they will be analyzed in their randomized group. If appropriate, a subgroup analysis will be performed comparing patients of the control with and without switch to Certican treatment including a further analysis comparing the subgroups to the randomized Certican group. If treatment will be modified in the Certican group, they will be analyzed as randomized.

Additionally to the analyses of data from the interval between Week 7 (BL2) and Month 6, the GFR according to Cockcroft-Gault will also be evaluated for the interval between BL1 and Month 6 analogous to the primary analysis for the FAS. No further sensitivity analyses will be performed for this time interval.

Results from supportive analyses will be interpreted in an explorative manner.

## **10.5 Analysis of secondary objectives**

### **10.5.1 Efficacy (secondary)**

The following secondary efficacy variables will be analyzed in an explorative manner for the full analysis set (FAS):

- Renal function as assessed by Nankivell and MDRD at Month 6 after Tx
- Serum creatinine at Month 6 and creatinine slope (1/serum creatinine versus time) between baseline and Month 6
- Occurrence of biopsy proven acute rejection, graft loss, or death at Month 6 after Tx
- Occurrence of treatment failure defined as composite endpoint of biopsy proven acute rejection, graft loss, death, loss to follow up, discontinuation due to lack of efficacy or due to adverse event, or conversion to another regimen up to or at Month 6 after Tx.

Additionally to the analyses of data from the interval between BL2 (Week 7) and Month 6, all secondary outcome criteria will also be evaluated exploratorily for the interval between BL1 and Month 6.

**Renal function:**

Glomerular filtration rate (GFR) will be computed according to Nankivell and MDRD method, respectively, and assessed at Month 6 post Tx by an ANCOVA model analogous to the primary analysis. Descriptive summary statistics will be provided by treatment group and visit.

Furthermore, serum creatinine at Month 6 will be analyzed by an ANCOVA model analogous to the primary analysis.

The creatinine slope (1/serum creatinine versus time) will be determined from all assessments between baseline and Month 6 using a linear regression model.

**Event data:**

Event rates will be estimated using the Kaplan-Meier method to handle adequately patients who discontinue the treatment prior to suffering from an event. Kaplan-Meier curves will be displayed graphically. The two groups will be compared using the logrank test. The following events or combination of events will be considered:

- Biopsy proven acute rejection (BPAR), defined as a rejection which was acute and proven by biopsy.
- Graft loss (GL)
- Death
- Treatment failure (composite endpoint) is defined as BPAR or GL or death or loss to follow-up or discontinuation due to lack of efficacy or adverse event or conversion to another regimen.

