## 2 Study purpose

This study wants to address the following question: Is a CNI-free regimen six weeks after transplantation for ESP patients as safe and well tolerated as standard treatment optimised for immunosuppression (benefit in renal function, NODM, CV risk, cancer, allograft nephropathy)?

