## **6.3 Treatment assignment**

A randomization list will be produced by or under the responsibility of Novartis Biometrics Department using a validated system that automates the random assignment of treatment groups to randomization numbers in the specified 2:1 ratio (Certican®, Control). Two sets of randomization numbers will be prepared for stratified randomization, one set for the group of patients who did not experience any rejection between Baseline 1 and Baseline 2 (Visit 3/Week 7) and one set for the group of patients who did experience at least one rejection in this period. Randomization numbers will be different in the two sets. The randomization scheme will be reviewed and locked after approval. According to the recommendations given in the ICH E9 Guideline "Statistical Principles for Clinical Trials" (CPMP, 1998), the used block length is specified in a separate document which is withheld from the study centers. The randomization list will be kept sealed in a secure location.

At Baseline 1 which has to be performed prior to the transplantation surgery, patients will be assigned a unique patient identification by the investigator. The patient identification has two parts. The first part is the four-digit center number, which is assigned by Novartis. The second part will be assigned by the investigator starting with number "00001" in each study site. Once assigned to a patient, the patient identification will not be reused. If the patient fails to be randomized for any reason, the patient's identification and the reason for not being randomized will be entered on

the Study Completion Page. Note: The patient identification is different from the randomization number.

At Baseline 2 (visit 3, Week 7), all eligible patients will be given a randomization number that assigns them to one of the treatment groups. The randomization numbers are sequentially allocated to the patients per center in the order of inclusion in the randomized treatment period. Each patient will receive only that treatment regimen which is labeled with the randomization number allocated to him/her.

Randomization of individual patients will be performed centrally by the designated CRO. Allocation of a patient to one of the two treatment groups will be performed in the following steps.

1. Information about patient inclusion (BL 1)  
Study sites will inform the randomization department of the designated CRO about each patient inclusion via fax

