#### Graft loss

The allograft will be presumed to be lost on the day the patient starts dialysis and is not able to subsequently be removed from dialysis. If the patient undergoes a graft nephrectomy, then the day of nephrectomy is the day of graft loss. This will be reported on the Premature Discontinuation of Study Medication CRF if medication is discontinued prematurely. The reason for graft loss will be recorded on the Graft Loss CRF. If graft loss occurs after the patient has discontinued study medication, the appropriate Follow-Up CRF should be completed. Graft loss is considered a Serious Adverse Event and should be reported on the Serious Adverse Event Case Report Form, which should be faxed to Novartis.

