## **11 Discussion and rationale for study design features**

The study design includes an initial phase of 6 weeks with an Sandimmun® Optoral based immunosuppressive regimen which is required by clinical needs. Dose adjustments after randomization to the treatment regimens in the CNI-free group follows experience from previous clinical trials with everolimus (see [Section 1](#) of this protocol).

Blinding of the two study treatments was not reasonable in this trial because dosing of Sandimmun® Optoral and Certican® has to be based upon trough levels. Therefore the study has to be planned open-label. However, the endpoint of the study is GFR which is an objective outcome variable depending on laboratory measures. An influence of open-label treatment on this primary outcome variable is limited because dosing behavior will mainly be governed by drug trough levels but only in a few expected cases of overt renal toxicity by the creatinine level.

Because early cyclosporine withdrawal in previous studies was associated with better renal function, but slightly increased frequency of rejection, cyclosporine withdrawal in this study is attempted with the additional application of 2 doses of Basiliximab. It is to be expected that the immunological risk at this point in time is low, and the benefit of cyclosporine elimination will continue. For this purpose, a CNI-free regimen will be compared with a standard Sandimmun® Optoral based immunosuppressive regimen. It is expected, that the CNI-free regimen will result in a

superior renal function and that the CNI-free are as safe and effective as the standard Sandimmun® Optoral-based regimen with regard to occurrence of biopsy proven acute rejection episodes, graft loss, death, and lost to follow up, as well of treatment failure (composite endpoint).

A maintenance treatment period of 18 weeks under both regimens is considered sufficiently long to explore any meaningful differences between the groups in the glomerular filtration rate, which is the primary efficacy outcome measure. This has been confirmed in previous clinical trials, where CNI-withdrawal led to an immediate and significant improvement of renal function within a few weeks. The design chosen for this study was also used in other switch studies ([Johnson et al., 2001](#); [Flechner et al., 2002](#)).

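### The stated reason for Kaplan-Meier implies censoring rejection, graft loss and death at treatment stop, against the as-assigned FAS and the follow-up planned after stopping

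*Protocol*

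**What the plan says.** Section 10.5.1 (Event data) treats BPAR, graft loss, death and a treatment-failure composite as time-to-event outcomes. The reason for the method is: "Event rates will be estimated using the Kaplan-Meier method to handle adequately patients who discontinue the treatment prior to suffering from an event". The comparison is one sentence: "The two groups will be compared using the logrank test". No censoring time, strata or interval for the difference is given. The composite also counts loss to follow-up and "discontinuation due to lack of efficacy or adverse event or conversion to another regimen" as events.

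Other sections bear on this:

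- Section 10.5.1 assigns the secondary efficacy variables to the FAS and calls them exploratory. Section 10.1 analyzes the FAS by assigned treatment and actual stratum.
- Section 6.5.6 says that patients who stop treatment early are not regarded as withdrawn from the study.
- Section 7 (Visit 7) asks for the Week 24 assessments soon after stopping and again six months after transplantation. They include rejections and biopsies since the last visit.
- Section 7.5 on graft loss: "If graft loss occurs after the patient has discontinued study medication, the appropriate Follow-Up CRF should be completed".
- Section 6.3, on rejection between the two baselines: "Two sets of randomization numbers will be prepared for stratified randomization". The ANCOVA in Section 10.4.2 includes that factor.
- Section 2 asks: "Is a CNI-free regimen six weeks after transplantation for ESP patients as safe and well tolerated as standard treatment". Section 11 expects that "the CNI-free are as safe and effective as the standard" regimen with regard to BPAR, graft loss and death, and Section 1 says much the same.

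**The concern.** A patient who has stopped treatment but is still followed needs no special handling in a Kaplan-Meier analysis; he or she simply stays at risk. Naming treatment discontinuation as the thing to be handled therefore points to censoring at the stop. The protocol would then collect later rejections, graft losses and deaths and leave them out of the curves meant to show them.

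Such censoring is harmless only if patients who stop have the same later hazard as those who continue. Section 6.5.6 lists adverse events, abnormal laboratory values and unsatisfactory effect among the reasons for stopping, so that cannot be taken for granted. Rejection is also the known risk of the strategy: Section 1 quotes an earlier cyclosporine-withdrawal study with BPAR of 4.2% against 9.8%, in favor of the CNI-containing arm.

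The second stake is interpretation. The protocol expects comparability on these events, but the only comparison it names is a test for a difference.

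**Working it through.** **1. Which end of risk does the text support?** The reason given for Kaplan-Meier points to treatment stop. The FAS as assigned, Section 6.5.6, the repeat Month 6 assessment and the Follow-Up CRF all point to observation until Month 6. The two cannot both govern the curves.

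**2. What censoring at the stop does.** The protocol gives no stopping rates or later hazards, so these inputs are assumptions: on-treatment risk 10% in both arms from Week 7 to Week 24, stopping s = 30% (Certican) and 15% (control), constant hazards, and hazard multiplied by m after stopping.

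Let L = −ln(0.90) = 0.1054, D = −ln(1 − s) and a = L + D − mL. Then

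true risk = 1 − exp(−(L + D)) − D × exp(−mL) × [1 − exp(−a)]/a.

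With censoring at the stop, Kaplan-Meier estimates the on-treatment risk, 10.0%, in both arms whatever m is.

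For m = 3:

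- Certican: D = 0.3567, a = 0.1459; 1 − 0.6300 − 0.3567 × 0.7290 × 0.9304 = 0.128.
- Control: D = 0.1625, a = −0.0482; 1 − 0.7650 − 0.1625 × 0.7290 × 1.0245 = 0.114.

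| Hazard after stop | True risk, Certican | True risk, control | Shown if censored at stop |
|---|---|---|---|
| m = 0.5 | 9.2% | 9.6% | 10.0% in both |
| m = 1 | 10.0% | 10.0% | 10.0% in both |
| m = 3 | 12.8% | 11.4% | 10.0% in both |
| m = 5 | 15.2% | 12.5% | 10.0% in both |

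A simulation at 162 and 82 patients agrees within simulation error: 12.9% and 11.3% for m = 3, 15.3% and 12.6% for m = 5, and no bias for m = 1. The between-arm difference lost is about 1.5 points for m = 3 and 2.7 points for m = 5. For m = 0.5 the sign reverses.

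**3. What the interval can show.** The plan gives no figure for the event endpoints; Section 10.7 sizes the trial for GFR only. With 162 and 82 patients and equal rates p, the 95% half-width is 1.96 × √[p(1 − p)(1/162 + 1/82)]:

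- p = 10%: 1.96 × √(0.09 × 0.018368) = 1.96 × 0.04066 = 8.0 points.
- p = 4.2%: 5.3 points. p = 9.8%: 7.9 points.

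Section 5 gives 164 for the Certican arm instead of 162; the half-width at 10% stays 8.0 points.

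**4. What a non-significant log-rank would mean.** Take the 4.2% and 9.8% quoted in Section 1 as a scenario only (that study used sirolimus and other time points). The hazard ratio is ln(0.902)/ln(0.958) = 2.40. Expected events are 82 × 0.042 + 162 × 0.098 = 19.3. By the Schoenfeld formula, √(19.3 × 2/9) × ln(2.40) − 1.96 = 1.82 − 1.96 = −0.14, which is a power of about 44%. An excess of that size would more likely than not be missed.

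**The case against.** The strongest reply is that the protocol never says patients are censored at treatment stop, that detailed censoring rules usually sit in the SAP, and that the FAS principle and the planned follow-up already favor counting all events. It stands that the censoring is implied, not stated. But the sentence fixes a rationale in the protocol that contradicts those other sections, so the conflict should be settled there.

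Four stronger readings are tempting and not supported:

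- **That failures are hidden.** The composite counts stops for lack of efficacy or adverse event, conversion and loss to follow-up as failures. Under Section 6.5.6, graft loss and severe rejection themselves force a stop, so those events come first and are counted. What remains is that the composite mixes tolerability with rejection and cannot show whether BPAR, graft loss or death rose. The safety tables do not fill the gap: rejections go on the Rejection CRF only (Section 7.5), and adverse events 7 or more days after stopping are left out of the summaries (Section 10.5.2).
- **That the bias runs toward showing no excess.** Size and direction depend on the hazard after stopping. If patients who stop everolimus return to a CNI, their rejection hazard could fall, and the error would change sign.
- **That the log-rank is unstratified.** The protocol is silent, and Section 10.1 refers to the actual stratum.
- **That equivalence is claimed from a non-significant test.** Section 2 speaks of safety and tolerability. Comparable effectiveness is an expectation in Sections 1 and 11, the event analyses are exploratory, and Section 10.4.2 limits confirmatory testing to GFR. Nothing says that non-significance will establish similarity.

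Regular safety review by the monitoring board protects patients during the trial but does not change how the final curves are built.

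**Conclusion.** The point holds as an internal conflict: the stated reason for Kaplan-Meier implies censoring BPAR, graft loss and death at treatment stop, while the analysis set and the follow-up rules imply observation to Month 6. If the implied rule were applied, events after stopping would drop out of the single-event curves, and the estimates would be biased whenever the hazard changes after stopping. The protocol does not allow the size or direction to be determined. On the assumed rates, the lost difference is 0 with an unchanged hazard and 1.5 to 2.7 points with a three- to fivefold hazard, within a half-width of about 8 points at a 10% rate. The composite mitigates this in part.

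The half-width comes from a sample sized for GFR and would not shrink under another censoring rule. It does show that a non-significant log-rank should not carry a statement of comparability. As these are exploratory secondary analyses, the change is advisable and nearly free; the primary analysis is not affected.

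**What to change.** Reword Section 10.5.1 (Event data) as follows:

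1. BPAR, graft loss and death are counted from randomization to Month 6 in all FAS patients, regardless of treatment discontinuation. Censoring occurs only at last contact or end of observation.
2. The log-rank is stratified by rejection between BL1 and BL2, matching the randomization and the ANCOVA.
3. The difference in Month 6 Kaplan-Meier rates is reported with a two-sided 95% confidence interval.

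State in Sections 1 and 11 that any comparability of the regimens on these events is judged from that interval and not from a non-significant log-rank.

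Sections 6.5.2 and 6.5.5, which speak of withdrawing patients from the study after long interruptions, must also be reconciled with Section 6.5.6, because they bear on who is followed to Month 6.

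The cost is wording in the protocol and SAP, since collection of events after stopping is already planned. The downside is a more cautious exploratory efficacy message.
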